## Procedure(s) to Account for Missing or Spurious Data

No imputation was made for missing data.

# MONITORING, AUDIT & INSPECTION

The investigator will permit study-related monitoring, audits and inspections by the Sponsor as required. This study will not be routinely monitored by the Sponsor, in accordance to the low risk nature of the study, but may be subject to audit for the QA team within the R&D department.

.

# ETHICAL AND REGULATORY CONSIDERATIONS

## Assessment and Management of Risk

As part of the Sponsor’s review process for all research projects, the study has been risk assessed according to their SOP. This study has been assessed as low risk.

## Peer review

The study protocol was peer reviewed by [name], co-investigator of the study.

## Public and Patient Involvement

Patient has been involved in the design of protocol and will be involved in result and dissemination of the findings

## Research Ethics Committee (REC) & Regulatory Considerations

The study will be conducted in compliance with the approved protocol and the Declaration of Helsinki. The protocol and all related documentation (e.g. informed consent form, participant information sheet, questionnaires) have been reviewed and received approval by a Research Ethics Committee (REC). The investigator will not begin any participant activities until approval from the HRA and REC has been obtained and documented. All documentation and correspondence must be retained in the trial master file/investigator site file. Substantial amendments that require HRA and REC (where applicable) review will not be implemented until the HRA and REC grants a favourable opinion (with the exception of those necessary to reduce immediate risk to participants).

It is the responsibility of the CI to ensure that an annual progress report (APR) is submitted to the REC within 30 days of the anniversary date on which the favourable opinion was given, annually until the study is declared ended. The CI is also responsible for notifying the REC of the end of study (see Section 6.9) within 90 days. Within one year of the end of study, the CI will submit a final report with the results, including any publications/abstracts to the REC.

Before any site can enroll a patient into the study confirmation of capacity must be sought from the site’s research and development (R&D) department. In addition for any amendment that will potentially affect the site’s permission, the research team must confirm with the site’s R&D department that permission is ongoing (Section 11.10).

## Protocol Compliance / Non-compliance Reporting

The investigator is responsible for ensuring that the study is conducted in accordance with the procedures described in this protocol. Prospective, planned deviations and/or waivers to the protocol are not acceptable, however accidental protocol deviations (non-compliances) may happen and as such these must be recorded. Non-compliances should be recorded in the CRF and/or a non-compliance log kept in the ISF. All non-compliances should be reviewed and assessed by the PI (or appropriately delegated individual) to determine if they meet the criteria of a “serious breach” (Section 12.6). Non-compliances which are found to frequently recur are not acceptable, will require immediate action, and could potentially be classified as a serious breach.

## Notification of Serious Breaches to GCP and/or the Protocol

A “serious breach” is a departure from the protocol, Sponsor procedures (i.e. SOPs), or regulatory requirements which is likely to effect to a significant degree –

- 1. The safety or physical or mental integrity of the subjects of the study; or
  2. The scientific value of the study.

If the PI (or delegate) is unsure if a non-compliance meets these criteria, they should consult the Sponsor for further guidance.

If a serious breach is identified the investigator should notify the Sponsor immediately (i.e. within 1 working day) using the ‘Non-CTIMP Notification of a Serious Breach’ form. The report will be reviewed by the Sponsor and CI, and where appropriate, the Sponsor will notify the REC within 7 calendar days of being made aware of the breach.

## Data Protection and Patient Confidentiality

The study will be conducted in accordance with the Data Protection Act 2018. The investigator will ensure that participant’s anonymity is maintained throughout the study and following completion of the study. Once the final dataset has been created the data will be pseudo-anonymised, with each patient given a study ID with no patient identifiable data

All documents will be stored securely with access restricted to study staff and authorised personnel.

[name] will act as the custodian of the data generated in the study.

## Financial and Other Competing Interests for the Chief Investigator, Principal Investigators at Each Site and Committee Members for the Overall Study Management

The researchers declare no conflict of financial or other competing interest

## Indemnity

As UHDB is acting as the research Sponsor for this study, NHS indemnity applies. NHS indemnity provides cover for legal liabilities where the NHS has a duty of care. Non-negligent harm is not covered by the NHS indemnity scheme. UHDB, therefore, cannot agree in advance to pay compensation in these circumstances. In exceptional circumstances an ex-gratia payment may be offered.

## Amendments

If changes to the study are required these must be discussed with the Sponsor, who is responsible for deciding if an amendment is required and if it should be deemed substantial or non-substantial. Substantial amendments will be submitted to the relevant regulatory bodies (REC, HRA) for review and approval. The amendments will only be implemented after approval and a favourable opinion has been obtained. Non-substantial amendments will be submitted to the HRA for their approval/ acknowledgment. Amendments will not be implemented until all relevant approvals are in place.

## Access to Final Study Dataset

[name] will have the access to final dataset which will be pseudo-anonymised.

# DISSEMINATION POLICY

## Dissemination Policy

The data is owned by UHDB NHS Trust and on completion of the study, the data will be analysed and tabulated and a Final Study Report prepared.

- The full study report can be accessed from the chief investigator.
- Participating investigators will have rights to publish any of the study data after discussion with the chief investigator.
- UHDB NHS Trust who sponsored the study will be acknowledged within the publications.
- The study protocol, full study report, pseudo-anonymised participant level dataset, and statistical code for generating the results will be made publicly available on clinicaltrials.gov after ethics approval.
- The study will be reported using the STROBE checklist for observational studies
- Limitation of the study includes –
  - Retrospective nature of the study
  - No urinary chemistry will be available
  - Sampling bias as ethnicity in Derbyshire & Staffordshire may have lower proportion of black population and the results may not be generalizable to other areas
  - Long-term effect of COVID-19 on AKI wont be available
  - Unmeasured confounders was dealt with COVID negative AKI control group where exposure to COVID-19 is not expected to be related to the outcome. This would address the potential magnitude of uncontrolled confounding

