**STUDY PROTOCOL**

# BACKGROUND

On 31^st^ December 2019, a cluster of pneumonia cases were detected in Hubei province of China where the cause was unclear. The cause for these cases was subsequently identified as a virus which was referred to as SARS-CoV-2, and the associated disease as COVID-19.^1^ This evolved rapidly into a global pandemic with first case reported in UK as early as on 30^th^ January 2020.^2^ As of 30^th^ April 2020, there have been 3.05 million laboratory confirmed cases world-wide with 161,145 cases in United Kingdom in 539,768 cases tested for COVID-19.^3^ The epidemiology of COVID-19 has differed in China, US and Italy which have different demographic characteristics, testing methods and different ways to curb the spread of infection which can be altered by many things, including behaviour, and the stringent social distancing measure.^4-7^ Though the pandemic started in China, as of 30^th^ April 2020, it has reported only 58.32 cases per million people (pmp) as compared to United kingdom which has reported 2433.8 cases pmp.^3^ This has resulted in different epidemiology of COVID-19 and organ system involvement. Lung involvement in the form of alveolar haemorrhages and respiratory failure has been well document in patients with COVID-19 and has been focus of attention, however, other organs are also affected in COVID-19, but there has been limited information kidney involvement in COVID patients.^5,8^ In initial reports, the acute kidney injury (AKI) incidence in COVID-19 has ranged from 5% to 29% with substantial variation between centres,

possibly due to differences in population demographics and risk factors for AKI.^1,2,5-7^ Initial reports on a small number of patients suggest that SARS-CoV-2 may have a specific effect on the kidneys but it is not yet clear to what extent COVID-19 increases the risk of AKI or how COVID-19 impacts outcomes after AKI.^8,9^

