## Outcome

The primary outcome is acute kidney injury in patients with COVID-19 disease.

Secondary outcomes will include all-cause mortality, need for ventilatory support, admission to ICU, length of stay.

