### Analysis Groups

Descriptive analysis will be performed in patients with COVID-19 disease between patients who didn’t have AKI with those who had AKI in COVID-19 disease, between AKI in COVID-19 disease and a control group of patients with AKI with no COVID-19 disease and between survivors and non-survivors in COVID-19 disease. For this, categorical variables will be described as frequency and percentages. Continuous variables will be described as mean with standard deviation or median with inter-quartile range. Means for continuous variable will be compared using t-test if the data is normally distributed otherwise Mann Whitney test will be used. Proportion from categorical variables will be compared with chi square test.

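### The protocol says a COVID-negative AKI control group deals with unmeasured confounding; that group is selected on the primary outcome and compared without adjustment, so the claim should be withdrawn

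*Protocol*

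**What the plan says.** Among the limitations in Dissemination Policy (12.1), the protocol says: "Unmeasured confounders was dealt with COVID negative AKI control group where exposure to COVID-19 is not expected to be related to the outcome". The next sentence reads: "This would address the potential magnitude of uncontrolled confounding".

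Outcome (3.2) fixes the endpoint: "The primary outcome is acute kidney injury in patients with COVID-19 disease". Analysis Groups (9.2.4) lists three descriptive contrasts. The first is within COVID-19 patients, those with AKI against those without. The second is "between AKI in COVID-19 disease and a control group of patients with AKI with no COVID-19 disease". The third is survivors against non-survivors within COVID-19. The methods named there are: "Means for continuous variable will be compared using t-test if the data is normally distributed otherwise Mann Whitney test will be used" and "Proportion from categorical variables will be compared with chi square test".

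The Background (1) names as open that "it is not yet clear to what extent COVID-19 increases the risk of AKI or how COVID-19 impacts outcomes after AKI". The Objectives (3.1) are narrower: to describe the epidemiology of AKI associated with COVID-19, and to study associations between characteristics and outcomes among patients admitted with COVID-19.

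**The concern.** The limitations wording borrows the logic of a negative control: an exposure or outcome that shares the confounders of the main comparison but has no causal link of its own, so that any association seen there must be bias. Swab-negative AKI patients are not that. They differ from the other group on the exposure of interest itself, and everyone in both groups has the outcome of interest. A difference between the groups could come from COVID-19, from measured confounders, from unmeasured confounders or from the selection on AKI, and the planned tests cannot separate these.

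What is at stake is interpretation. A published limitations section saying that confounding was handled invites readers to take crude differences between COVID-positive and COVID-negative AKI patients as effects of COVID-19.

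**Working it through.** The only design figure stated is 330 AKI patients (Study Summary). It has no effect size, power or precision target behind it, so there is nothing to reproduce, and the point does not depend on it. The check is one of design logic, with illustrations whose assumed inputs are marked.

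**1. Is any adjusted COVID-status comparison planned?**

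| Section | Population | COVID status as exposure? |
|---|---|---|
| 9, opening paragraph: AKI incidence with 95% CI | COVID-positive only | No |
| 9.2.2: mortality model | Framed in COVID-19 disease | No |
| 9.2.2: AKI model | COVID-19 disease | No |
| 9.2.4: COVID AKI against non-COVID AKI | AKI patients only | Yes, unadjusted |

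The only contrast by COVID status is unadjusted and restricted to AKI cases.

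**2. Can it show AKI risk by COVID status?** With a and b AKI cases among N+ and N− admissions, RR = (a/N+)/(b/N−). The contrast supplies a and b but not N+ or N−. Assume the 330 split 165/165, and let incidence in each group range over the 5% to 29% that the Background gives for COVID-19 (applying it to negatives is an assumption):

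- 29% against 29%: N+ = N− = 165/0.29 = 569, RR = 1.0.
- 29% against 5%: N+ = 569, N− = 165/0.05 = 3,300, RR = 5.8.
- 5% against 29%: N+ = 3,300, N− = 569, RR = 0.17.

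The same case counts fit all three.

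**3. Does the crude test remove or measure unmeasured confounding?** Assume COVID-19 has no effect on death among AKI patients, and an unmeasured factor U gives 50% mortality when present and 20% when absent. Crude mortality in a group is 0.5u + 0.2(1 − u), where u is the prevalence of U. With 165 per group, the chance of p<0.05 is about Φ[(Δ − 1.96·SE0)/SE1], where Δ is the difference in mortality, SE0 the pooled standard error and SE1 the unpooled one.

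| U in the two groups | Crude mortality | RR | Chance of p<0.05 |
|---|---|---|---|
| 50% vs 40% | 35% vs 32% | 1.09 | about 8% |
| 60% vs 30% | 38% vs 29% | 1.31 | about 41% |
| 70% vs 30% | 41% vs 29% | 1.41 | about 63% |

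For the middle row, Δ = 0.09, SE0 = 0.0520 and SE1 = 0.0517, so Φ(−0.23) = 0.41. Nothing in the planned output would tell the reader that U was responsible.

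**4. What does selecting on AKI do?** Let another cause of AKI, S, be present in 40% of admissions whatever their COVID status, and let r(c,s) be AKI risk. Among AKI patients the odds of S are (0.4/0.6) × r(c,1)/r(c,0). They are equal in the two groups only if r(1,1)/r(1,0) = r(0,1)/r(0,0), that is, if the risks multiply exactly. Assume death depends on S alone: 15% without S and odds ratio 3 with it. The odds with S are 3 × 0.15/0.85 = 0.529, a risk of 34.6%.

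| Assumed AKI risk: neither / COVID only / S only / both | AKI incidence, + vs − | S among AKI, + vs − | Death, + vs − | Crude death OR |
|---|---|---|---|---|
| 4 / 8 / 12 / 24% (multiplicative) | 14.4% vs 7.2% | 66.7% vs 66.7% | 28.1% vs 28.1% | 1.0 |
| 5 / 10 / 20 / 25% (additive) | 16% vs 11% | 62.5% vs 72.7% | 27.3% vs 29.3% | 0.91 |
| 4 / 25 / 30 / 47.5% | 34% vs 14.4% | 55.9% vs 83.3% | 26.0% vs 31.3% | 0.77 |

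Last row in full:

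- Incidence: 0.6×0.25 + 0.4×0.475 = 0.34, and 0.6×0.04 + 0.4×0.30 = 0.144.
- S among AKI: 0.19/0.34 = 0.559, and 0.12/0.144 = 0.833.
- Death: 0.441×0.15 + 0.559×0.346 = 0.260, and 0.167×0.15 + 0.833×0.346 = 0.313.
- OR: (0.260/0.740)/(0.313/0.687) = 0.77.

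In every row COVID-19 has no effect on death given S.

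**The case against.** The strongest defence is that the study does not set out to estimate the effect of COVID-19 on AKI risk. That question appears in the Background; the Objectives are descriptive and associational, and Analysis Groups labels the contrast descriptive. This stands. A reader might infer that the study fails its own aim because it cannot show whether COVID-19 raises AKI risk, or that leaving out swab-negative patients without AKI is an error. The Objectives do not support either inference; the omission is a missed opportunity.

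Three further inferences should also be resisted. One is that AKI-only data look the same whatever COVID-19 does to AKI risk. They need not, since the mix of other causes can shift, as in the last two rows of step 4; what holds is that the risk is not identified. Another is that selection on AKI always biases the later comparison. It does not if risks multiply exactly, and the 0.77 rests on one scenario whose 34% incidence in positives lies above the 29% upper end given in the Background. The third is that the premise of no expected relation to the outcome flatly contradicts the Background. The limitations text does not say which outcome is meant, and an assumption about an open question is unjustified rather than contradictory.

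A separate SAP might add covariates. That would deal with measured confounders only and would not make the sentence about unmeasured ones true. The reference to potential magnitude softens the claim but does not rescue it, because the contrast yields no measure of bias.

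**Conclusion.** The claim is wrong as written. The group is selected on the primary outcome, is not a negative control and is compared without adjustment, so it neither deals with unmeasured confounding nor measures it. This part rests on the protocol's text alone.

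The size of any distortion is not known from the document. The odds ratios of 1.0, 0.91 and 0.77 depend on assumed AKI risks, on a 40% prevalence of S unrelated to COVID status, and on an assumed death model; they show that the amount varies with how causes combine. As a description of how the two AKI groups differ, the contrast is sound.

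Severity is moderate. The AKI incidence in COVID-positive patients and the models within COVID-19 do not use this group and are unaffected.

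**What to change.** **Needed.** Delete the two limitations sentences on unmeasured confounders in Dissemination Policy. State instead that residual and unmeasured confounding remain, and that the comparison of AKI with and without COVID-19 is descriptive and conditional on having AKI.

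**Only if the contrast is to inform the Background questions.**

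- Report AKI incidence with 95% CI in all eligible swab-positive and swab-negative admissions.
- Fit a logistic model for AKI with COVID status as exposure, adjusted for baseline variables already collected, such as age, gender, ethnicity and comorbidities.
- Adjust the mortality comparison among AKI patients in the same way, labelled as conditional on AKI.
- An E-value for residual confounding is optional.

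**Cost.** The needed change is a rewording, and the limitations statement becomes less favourable. The further analysis is modest: Inclusion Criteria (6.1) admits adults with a swab result whichever way it falls, and Patient Identification (7.1.1) and Data Workflow (8.3) already plan the linkage.

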# APPENDICES

## Appendix 2 – Amendment History

| **Amendment No.** | **Protocol version no.** | **Date issued** | **Author(s) of changes** | **Details of changes made** |
| --- | --- | --- | --- | --- |
| 1 | 1.1 | 27/May/2020 | NK | Updates to study design and statistical analysis plan following peer reviewer comments.  Updates to the study dates to reflect actual dates. |

Detail all protocol amendments. Protocol amendments must be submitted to the Sponsor for approval prior to submission to the REC.
